### Risks and anticipated benefits for trial participants and society including how benefits justify risks

There are potential risks linked to offering financial incentives for patients in the intervention group. These include that patients a) become financially dependent on the incentive, b) demand more money over time, c) will not want to terminate the scheme although they might be prepared to adhere to medication even without the incentive, and d) spend the additional income on illegal drugs. Also, other patients who have been adherent so far might ask to be offered financial incentives as well and/or decrease their adherence to become eligible. Based on 5 years experience with the intervention in the AOT in the East London Borough of Newham, one can expect most of these risks to be limited. No patient with good adherence has ever asked to receive financial incentives as well (and to our knowledge none has ever become poorly adherent in order to be eligible for the scheme). One patient receiving the intervention has once asked for the money to be increased which was declined without any negative consequences. The financial dependence is difficult to judge, but the maximum overall amount of £60 per 4 week period is rather small to induce dependence. We cannot guarantee whether patients spend the additional income on illegal drugs, but all patients have civil rights and the capacity to decide on what they want to spend their money and, on a practical level, the amount of incentives is not sufficient to fund a significant use of illegal drugs.

The anticipated benefits for the patient include a much better quality of life with reduced distress, lower suicide risk, fewer problems with the justice system, lower rate of compulsory treatment and less time spent in psychiatric in-patient units. Some patients may see the benefit of the medication, change their attitude towards it and later take it without financial incentives [23].

The potential benefits to society include a reduced risk of patients to harm others and much lower costs in terms of input of health services and other services in the society including the police and the justice system.

For patients in the control group there are no discernible risks or benefits. They will only be asked whether they consent to their data being used for research and would consider in principle an offer of financial incentives to take their medication. Their care will not be altered at all. For patients in either group there are a maximum of eleven satisfaction ratings on one scale, but no potentially distressing interviews or assessments. In the intervention group, patients get offered financial incentives, but can refuse further financial incentives and medication itself at any point of time.

### Trial Steering Committee and Data Monitoring Committee

A trial steering committee (TSC) will be established with an independent chair, a user representative, and at least two further independent experts.

Although the amount of data collection is limited in the trial, we will also establish a Data Monitoring and Ethics Committee (DMEC) because of the ethically sensitive nature of the intervention. The DMEC will be independent of the applicants and report to the TSC. It is suggested to have a joint TSC/DMEC meeting at the beginning of the study, and subsequently arrange DMEC meetings before the TSC meetings. The meetings of both groups will be scheduled for times immediately following the expected delivery of major milestones, i.e. in month 6, 12 and 25 of the study

### Ethical approval

The study has been approved by Ealing and West London Research Ethics Committee (REC reference number: 09/H0710/35). All data will be anonymised and stored securely in line with the Data Protection Act. No published data will contain patient identifiable information.

### Statistical analysis

For analysis, we will use generalized linear models as appropriate to the outcome, with random effects for groups, and sensitivity analyses to explore the impact for missing data. A detailed Statistical Analysis Plan will be agreed by the TSC prior to analysis of un-blinded data.

### Economic analysis

A cost-effectiveness analysis will be conducted from an NHS perspective, using data on health service use, national unit cost figures and the main outcomes in turn (adherence, time 'slippage' of taking depots, CGI). Incremental cost-effectiveness ratios and cost-effectiveness acceptability curves will be estimated and employed as necessary, generated from the net benefit approach and using bootstrap regression for a range of values of willingness to pay for incremental outcome changes. Sensitivity analyses will examine the impact of altering key assumptions and parameter values. It is usual in any trial to find differences in service access, treatment adherence, baseline characteristics, changes in outcome dimensions over time, cost and cost-effectiveness. In the present study, these variations would be of particular interest, and we therefore plan to analyse patterns within the samples in order to examine whether there are identifiable patterns of inequity with respect to need, socioeconomic group, and key demographic characteristics. The concentration index approach, now quite widely used in health economics for example, offers a robust and informative methodology [24].

### Proposed sample size

We will recruit 34 AOTs in England (initially 36 to allow for two teams to drop out between recruitment and beginning of trial), and 4 patients within each team. Seventeen teams each will be randomly allocated to the experimental group and the control intervention, i.e. 'treatment as usual'. We aim to have 68 patients in each arm of the trial, allowing for one patient per team to be lost between recruitment and one year follow up. This estimate of a loss of one patient per team may be rather pessimistic, but enables us to have a minimum of 52 patients per arm (assuming that in at least one team per arm there will be no loss to follow up) included in the intention-to-treat analysis. Dropping out of the study and the intention-to-treat analysis will occur only because of a) death, b) long-term imprisonment, c) long-term hospitalisation, d) unknown whereabouts with no chance to obtain outcome data, or e) withdrawal of consent for the data to be used for research. Patients in the intervention group may discontinue with the intervention within the one year study period, because their clinicians think that maintenance medication is not appropriate anymore or patients themselves decide to come off the scheme. Such patients will still be included in the intention to treat analysis, and discontinuing with the scheme will not compromise the availability of outcome data. Refer to Figure 1. CONSORT Flow Diagram for details.

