### Outcome measures

The primary outcome is adherence to anti-psychotic maintenance medication during the 12 month trial period. Adherence will be measured, objectively, as the percentage of prescribed depot injections actually taken. As the primary outcome, the percentage will be used as a continuous variable. However, we will also analyse the percentage in a dichotomised way, comparing the ratio of patients with 'good' adherence (i.e. =80% of prescribed depots taken [20]) in the two conditions.

Further secondary outcomes are:

a) The time 'slippage' of taking depots, defined as the percentage of the prescribed time interval that has expired before the depot is taken;

b) Clinical improvement as assessed on the Clinical Global Impression Scale (CGI) [21] by the treating consultant psychiatrist at the end of the 12 month period;

b) Number of involuntary and voluntary hospital admissions during the trial period;

c) Costs of care: data on the use and frequency of use of inpatient care, outpatient care (including home visits, home treatment), and other health services during the 12 month treatment period will be obtained from case notes and electronic administrative data bases. Costs for the intervention will be estimated for each participating team from information provided by staff. Established national unit costs will be used to estimate direct health care.

d) The number of attempted and completed suicides, incidences of physical violence, police arrests and days spent at work/training/education will also be recorded over the 12 month trial period.

e) Subjective quality of life and satisfaction with medication which will be assessed at the beginning and end of the intervention period using the 11 item scale established in the DIALOG trial [22]. The scale contains 11 items asking patients to rate their satisfaction with 8 life domains and 3 treatment aspects, one of which is medication, on a scale ranging from 1 (lowest satisfaction) to 7 (highest satisfaction).

f) Continuation with financial incentives (in intervention group only) and adherence during a 6 month follow up period will be taken from the medical records.

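### The intention-to-treat set drops randomised patients for death, long-term imprisonment or long-term hospitalisation even when their records exist, and this conflicts with the listed outcomes

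*Protocol article*

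**What the plan says.** Under Methods, Proposed sample size, the protocol article gives the rule for leaving the analysis: "Dropping out of the study and the intention-to-treat analysis will occur only because of a) death, b) long-term imprisonment, c) long-term hospitalisation". The list goes on: "d) unknown whereabouts with no chance to obtain outcome data, or e) withdrawal of consent for the data to be used for research". The condition that data cannot be obtained is attached to reason d) alone.

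The same paragraph keeps patients who come off the incentive scheme, or whose clinicians no longer think maintenance medication appropriate: "Such patients will still be included in the intention to treat analysis". It recruits 68 patients per arm and says that its allowance for loss "enables us to have a minimum of 52 patients per arm" in the intention-to-treat analysis.

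Four other parts of the article bear on the rule:

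- **Outcome measures.** Item d) reads "The number of attempted and completed suicides, incidences of physical violence, police arrests and days spent at work/training/education will also be recorded", over the 12-month trial period. One of the two items labelled b) is "Number of involuntary and voluntary hospital admissions during the trial period". Item c) collects inpatient care use for costing.
- **Design.** Patients are recruited before teams are allocated. The primary outcome and most secondary outcomes come from medical records.
- **Risks and anticipated benefits.** The benefits expected for patients include lower suicide risk, fewer problems with the justice system and less time as an inpatient.
- **Statistical analysis.** Sensitivity analyses for missing data are promised, with detail left to a later analysis plan.

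**The concern.** An intention-to-treat set keeps everyone who was randomised, whatever happens afterwards. Here three kinds of post-randomisation event take a patient out, and the plan expects the intervention to make events of these kinds rarer. If it does, the two retained groups are no longer the groups that were allocated, and the adherence comparison could be distorted.

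The same rule affects the secondary outcomes. A patient who dies by suicide leaves under reason a). A patient with a very long admission leaves under reason c), taking that admission and its cost along. At stake are the primary estimate, the rare-event outcomes and the cost-effectiveness analysis, which could lose its most expensive patients.

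**Working it through.** **1. The exclusion reasons against the rest of the article**

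| Reason | Excluded only if data are unobtainable? | Related outcome in Outcome measures | Expected to fall with incentives? |
|---|---|---|---|
| a) death | no | completed suicides | yes, suicide risk |
| b) long-term imprisonment | no | police arrests | yes, justice-system problems |
| c) long-term hospitalisation | no | admissions, inpatient costs | yes, inpatient time |
| d) unknown whereabouts | yes | none specific | not stated |
| e) consent for data use withdrawn | not needed | none | not stated |

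Reasons d) and e) are ordinary missing data. Reasons a) to c) are not. The primary outcome is a percentage of prescribed depots taken, so it can be computed from the records up to the event.

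**2. The plan's own count**

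Proposed sample size gives 17 teams per arm, 4 recruited per team, one lost per team, and no loss in one team.

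- Retained: 17 × 3 + 1 = 52 per arm, as stated.
- Allowed loss: 68 − 52 = 16, and 16/68 = 23.5%. This covers all five reasons.

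**3. Possible shift in the primary estimate (illustration)**

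From the plan: retained means of 65% (control) and 85% (incentive), a difference of 20 points. Assumed, because the article gives no figures: removed patients are g points less adherent than retained patients in their own arm, and k_C control and k_I incentive patients are removed.

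Difference in all 68 per arm = 20 − g × (k_I − k_C)/68.

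With g = 30:

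- 16 control, 8 incentive removed: control (52×65 + 16×35)/68 = 57.9; incentive (60×85 + 8×55)/68 = 81.5; difference 23.5. The analysed 20 is 3.5 too low.
- 8 control, 16 incentive removed: control (60×65 + 8×35)/68 = 61.5; incentive (52×85 + 16×55)/68 = 77.9; difference 16.5. The analysed 20 is 3.5 too high.
- 16 removed in each arm: 57.9 and 77.9; difference 20.0. No shift.

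For the 16 versus 8 split, g = 15 gives 15 × 8/68 = 1.8 points and g = 45 gives 5.3.

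Equal losses are harmless only if the gap is the same in both arms. Assume instead that removed patients average 30% in both arms:

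- 16 removed in each arm: 72.1 − 56.8 = 15.3 (analysed 20 is 4.7 too high).
- 16 control, 4 incentive: 81.8 − 56.8 = 25.0 (5.0 too low).
- 4 control, 16 incentive: 72.1 − 62.9 = 9.1 (10.9 too high).
- 4 removed in each arm: difference 18.8 (1.2 too high).

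If removed patients resemble those retained in their arm (g = 0), there is no shift at all.

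**4. Does keeping everyone cost power?**

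Power = Φ(20/(31 × √(2/n_eff)) − 1.96), with the plan's SD of 31, difference of 20 and ICC of 0.05. A two-sided 5% test is assumed.

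- 52 per arm, 3 per team: design effect 1 + 2 × 0.05 = 1.10; n_eff = 47.3; power 88.0%.
- 68 per arm, 4 per team: design effect 1 + 3 × 0.05 = 1.15; n_eff = 59.1; power 93.9%.

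This holds the SD and difference fixed. Shorter records give noisier percentages, so 93.9% is an upper guide.

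**The case against.** The strongest defence is that the paragraph sits under sample size and mainly explains how many patients will have one-year data. It keeps the group most often dropped wrongly, those who stop the intervention. Missing-data sensitivity analyses are promised, and the handling of partial follow-up normally belongs in an analysis plan that is not shown. Only long-term imprisonment and hospitalisation count, so ordinary arrests and admissions stay in. The loss allowance is described as possibly pessimistic, and loss is expected to be low.

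Much of this stands, and it limits what can be claimed. Four stronger readings are tempting but not supported:

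- **Completed suicides will be zero in both arms by construction.** Outcome measures says they will be recorded over the trial period. The two sections conflict; the article does not show which would be followed.
- **The comparison is biased.** No rate, adherence level or arm split for removed patients is given. That these events follow from non-adherence is the plan's expectation, and not every death or imprisonment does.
- **Patients who disappear are dropped although the team's record shows missed depots.** Reason d) applies only where outcome data cannot be obtained, so a patient whose record supplies the outcome stays in.
- **Nearly a quarter of patients may be removed for outcome-related reasons.** The 16 of 68 is a planning allowance that includes withdrawn consent. It runs from recruitment, so it may include losses before allocation.

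The defence does not rescue reasons a) to c). The article expressly names the intention-to-treat analysis as what these patients leave, and it does so whether or not data exist. That is a stated rule, not a detail left for later. A sensitivity analysis for missing data does not redefine a primary set from which patients are excluded by rule.

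**Conclusion.** The point holds for reasons a) to c). The set as defined is not intention-to-treat. Because the plan expects the intervention to affect these kinds of event, retention may depend on arm, which is a selection-bias risk of unknown direction and size. The figure of about 3.5 points either way on a 20-point difference is an illustration. It rests on an assumed 30-point gap and an assumed 16 versus 8 split; other assumptions in the working run from no shift to 10.9 points.

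Separately, and without any assumption about adherence, the rule read literally contradicts the outcome list on completed suicides. It would also remove the arrests, admissions and inpatient costs of excluded patients. Both defects should be settled before unblinded data are analysed.

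**What to change.** Replace the rule in Proposed sample size, and reconcile it with Outcome measures, as follows:

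1. Analyse every randomised patient in the arm of their team. Remove data only where consent for its use is withdrawn.
2. For reasons a) to c), compute adherence from the injection records available up to the event.
3. Count deaths, suicides, arrests, admissions and costs for everyone, up to and including the event, and allow for time at risk.
4. Treat patients under reason d) with no obtainable data as missing. Counting their depots as not taken is a worst-case single imputation and belongs in a sensitivity analysis.
5. Keep the present set as a sensitivity analysis.

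The cost is revised wording and use of event dates in the records, with no extra patients or visits. The drawback is partial follow-up: some percentages will rest on few prescribed depots, and stopping the count at the event still depends on something that happened after allocation. The analysis plan should say how it deals with both.

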**Figure 1 F1:**
[figure not shown]
**This figure displays the CONSORT Flow Diagram**.

According to the definition of good adherence as taking at least 80% of prescribed medication, the study is powered to detect a difference in adherence from 25% in the TAU arm to 65% in the experimental arm with 90% power for 5% significance. To convert this to a continuous measure requires an estimate of the standard deviation of the percentage of medication taken: Remington et al 2007 [20] estimate this as 31%. This estimate may appear high, which makes our power calculation rather conservative. Assuming the 31% standard deviation pertains to both arms, the original assumptions are then equivalent to assumed means of 60% of prescribed medicine on TAU, and 92% on treatment. In fact, the mean in Remington et al [20] was 66%, so the revised sample size calculations on the continuous measure are powered for a more modest increase from 65% to 85% (an absolute difference of 20%). This would require 47 per group in an individually randomised study. This then has to be inflated to allow for clustering. Assuming an ICC of 0.05 and an average of 3 patients per team gives an inflation factor of 1.1 [25] or 52 per group. We will therefore aim to have one year follow up data from at least 3 patients each from 17 teams per arm (and for 4 patients in one team in each arm). To allow for potential dropout we will actually recruit 4 per team. We do not propose a correction for variable group size. The numbers recruited per team are under our control and the loss to follow-up rate is likely to be low with small differences between teams. Thus, the coefficient of variation of the group sizes is unlikely to exceed 23% [26].

## Discussion

The trial aims to establish the effectiveness and cost effectiveness of offering financial incentives to improve adherence to antipsychotic maintenance medication. The target group are patients with psychotic disorders who do not adhere to medication, although they are likely to benefit from it. The primary outcome is adherence to medication. We assume that an improved adherence to medication will be associated with significant health and social gains for the patients concerned. However, the aim of this trial is only to test an intervention to improve adherence and not whether antipsychotic maintenance medication is indeed effective or not. We therefore decided to use health and social outcomes only as secondary criteria, although improving them is the ultimate objective of the whole intervention.

It would also have been desirable to have patient reported measures, e.g. on their attitude to treatment in general and to medication in particular, as a central outcome. However, the target group of this study are very difficult to engage in care and often even more difficult to engage in research trials. Requiring patients to attend interviews or fill in questionnaires may have limited recruitment and lead to substantial drop out rates. Thus, the ideal research design cannot be implemented because patients are likely not to comply.

We plan to conduct the study with and in AOTs. Yet, given the possible organisational changes in the NHS which can be difficult to anticipate, we may have to deal with teams that are re-configured during the duration of the trial. The research team will try and implement the study protocol despite such changes. We will aim to ensure that the allocation of patients to teams in the experimental arm or control group throughout the study period is not compromised. This may be a challenge since the research team has no managerial or clinical control over the participating clinical teams. We will also aim to assess the general experiences of teams with the practice, e.g. whether other hitherto adherent patients also asked for financial incentives and whether teams continue with offering financial incentives to the study patients after the end of the trial. These general experiences may be highly relevant for a potential wider implementation of the intervention.

If the trial shows that offering financial incentives is effective and cost-effective, it may be recommended as an option in the treatment of patients with psychotic disorders who are non-adherent to medication. The measure is not coercive and requires patients to have full capacity to make the decision to both taking the medication and accepting a financial incentive. There is no reliable data on the exact size of that group of patients. One may estimate that between 1000 and a maximum of 5000 patients in the UK may fall into this category at one point of time. However, the implications of a positive finding may go beyond the UK and also affect treatment of similar patients in other countries.

## List of abbreviations used

AOT: Assertive Outreach Team; CMHT: Community Mental Health Team; DMEC: Data Monitoring and Ethics Committee; FIAT: Financial Incentives (for) Adherence Trial; ICC: Intracluster Correlation Coefficient; NHS: National Health Service; TAU: Treatment As Usual; TSC: Trial Steering Committee.
